### Aims and hypotheses

This study aims to assess the physiologic sleep variables, masticatory functions of the bilateral masseter and anterior temporalis muscles, and salivary parameters by means of PSG, sEMG, and specific salivary tests (levels of cortisol, presence of *Pseudomonas aeruginosa*, salivary flow, and pH) respectively, prior to and after neuromuscular electrical stimulation (NMES), the mastication apparatus (MA), and the mandibular advancement oral appliance (OA_m_) in patients with DS. It is hypothesized that oxyhemoglobin desaturation, caused by sleep apnea events, can lead to harmful functions of the neuromuscular system in patients with DS, reducing muscle tonus, which in turn may facilitate obstruction of the upper airways. Moreover, sleep breathing disorders may also lead to sleep architecture fragmentation and increase the arousal index, causing fatigue, nonrestorative sleep, excessive daytime sleepiness, learning and memory difficulties, which may result in low performance in daily tasks, and alterations in the physiological patterns of the various systems of the organism, creating a scenario for the emergence of several comorbidities, including cardiovascular disease that is very common in these individuals. Looking at these problems, it is expected that the OA_m_ will promote a dimensional increase in the oral pharynx during sleep, favoring the airflow and allowing the elimination and/or reduction of snoring and of obstructive sleep apnea. The electrical activity of the masticatory muscles may also be modulated, contributing to reduce the nocturnal obstruction. Furthermore, it is expected that NMES and the MA will contribute to the balance of masticatory muscular functions by means of recruiting muscle fibers. This muscular recruitment will reduce hypotonia and adjust the functions to the physiologic patterns of electrical muscle activity, both in rest and in isometric positions [31, 32]. The samples will be divided according to the randomization rules into three groups: neuromuscular electrical stimulation (NMES), which will be applied to the individuals in Group 1 (DS-NMES); mastication apparatus (MA), which will be applied to individuals in Group 2 (DS-MA); and mandibular advancement oral appliance (OA_m_), which will be applied in individuals in Group 3 (DS-OA_m_). All clinical interventions will be carried out during a period of 2 months.

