#### Analysis of surface electromyography data

In order to obtain a frequency domain analysis, surface EMG signal processing will be carried out using specific routines conducted with the Matlab program, version 7.1 (The MathWorks Inc., Natick, MA, USA). In addition, the time domain analysis will be executed using the root mean square (RMS) of the EMG signal (expressed in μV) and will be normalized by the highest values of RMS obtained during the three MHI and MVC readings (μVmV/μV/100: % MVC). The data captured at rest (total of 15 s) will be used for both analyses during MHI and MVC (total of 3 s; the first and fifth seconds having been discarded).

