#### Phases of the surface electromyography examination

The sEMG, referring to the bilateral masseter (surface portion) and to the temporal (anterior portion) muscles in rest, MVC, MHI, and bite force, shall be carried out in two distinct phases: Phase 1, initial data acquisition, prior to proposed therapies (Groups 1–3); and phase 2, treated groups (Groups 1–3) after 2 months of neuromuscular electrical stimulation, mastication apparatus with mastication instrument Hiperboloide®, and mandibular advancement oral appliance therapies. The obtained data will be compared among each group and among each person with themselves, to verify the effectiveness of the proposed therapies on the improvement of the masticatory muscle electrical activity, on the physiological sleep variables, and on salivary parameters in patients with DS.

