#### Protocol for neuromuscular electrical stimulation

Neuromuscular electrical stimulation (NMES) will be used to improve and/or balance the muscular tonus and to modulate masticatory and oropharyngeal muscle functions. This method has proven to be a safe and effective therapy [15]. The Neurodyn Imbramed II equipment with a four-channel device will be used (Fig. 7). NMES is a noninvasive, safe, and effective treatment, which uses electrical impulses to stimulate and/or modulate a group of injured and/or altered muscle functions. It can also favor blood circulation, improve muscle spasms, reduce edema caused by inflammatory processes, and increase muscle strength, resulting in gain of the muscular tonus [20, 21]. The equipment will deliver a low-current intensity in order to induce action potentials in motor nerves, resulting in the activation of motor units [45, 46]. This therapy produces electrical stimulation on a group of muscles, through surface electrodes correctly placed on the muscles. NMES will be performed according to Guidelines 601 and 601-2-10 of the International Electrotechnical Commission, which establishes the rules for the respective usage of electromedical devices and electrical stimulators. The surface electrodes will be placed on the muscle motor point (bilateral masseter and anterior temporalis). The following parameters will be used: pulse frequency of 50 Hz, pulse width of 250 μs, on/off ratio of 5 s of stimulation and 10 s of rest for 20 min, and low-current intensity (range from 12 to 19 mA) per session, depending on patient sensitivity, and according to the protocol developed by Giannasi et al. [14, 15]. The patients will undertake three 20-min sessions per week of NMES on the bilateral masseter and the anterior temporalis muscles during a 2-month period. The described parameters may evoke muscle response with minimal discomfort to the patients, although most patients usually do not mention feeling any discomfort or pain. A visible muscle contraction will be noted when NMES is applied, meaning that the electrical stimulus produced the necessary contraction.

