## Discussion

This clinical trial will assess the physiologic sleep variables, masticatory function of the masseter and anterior temporalis bilateral muscles, and salivary parameters by means of PSG, sEMG, and specific salivary tests (cortisol levels, presence of *P. aeruginosa,* salivary flow, and pH) respectively, prior to and after mandibular advancement oral appliance (OA_m_), neuromuscular electrical stimulation (NMES), and mastication apparatus (MA) therapies in patients with Down syndrome. As the primary outcome, the authors believe that OA_m_, neuromuscular electrical stimulation, and mastication apparatus therapies may improve masticatory and oral pharynx muscle modulation, adjusting them to a level close to normality, which may lead to a balanced muscle activity contributing to reduce snoring/sleep apnea. Good sleep quality is likely to reduce corporal stress, as shown by the decrease in cortisol levels in the saliva, as a secondary outcome. In addition, the authors expect an improvement in other salivary parameters, as the absence of snoring and/or sleep apnea, which result from the act of breathing through their mouth, will contribute to the balance of the microorganisms in the oral cavity. Moreover, polysomnography will be used to evaluate the other sleep variables and the authors believe that sleep quality will improve after all therapies have been carried out. Another expected outcome is to measure the objective compliance and adherence to the OA_m_ with an embedded microsensor thermometer.

It is important to highlight that none of these therapies will cause any injuries to the participants, so the hypothesis of harm or of adverse side effects does not apply to the present study.

Neuromuscular electrical stimulation (NMES) may produce a feeling of discomfort due to the electrical stimulus applied on masticatory muscles; however, it does not offer foreseeable risks. The mastication apparatus (MA) does not produce discomfort or foreseeable risks. The mandibular advancement oral appliance (OA_m_) embedded with a thermosensitive microchip may initially produce discreet dental and muscular discomfort, with possible temporary hypersalivation and risks of occlusal changes. The polysomnography, surface electromyography, and specific salivary tests do not produce discomfort or foreseeable risks.

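### Muscle balance is one of the stated masticatory aims, but the only named EMG variable is amplitude, and tests on amplitude cannot show whether balance changed

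*Protocol article*

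**What the plan says.** Balance appears in three places as something the therapies should achieve.

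- Aims and hypotheses: "it is expected that NMES and the MA will contribute to the balance of masticatory muscular functions", through recruitment of muscle fibres. The next sentence gives the mechanism: "This muscular recruitment will reduce hypotonia and adjust the functions to the physiologic patterns of electrical muscle activity".
- Protocol for neuromuscular electrical stimulation: NMES "will be used to improve and/or balance the muscular tonus and to modulate masticatory and oropharyngeal muscle functions".
- Discussion, in the sentence on the primary outcome, about the masticatory and pharyngeal muscles: "adjusting them to a level close to normality, which may lead to a balanced muscle activity contributing to reduce snoring/sleep apnea".

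The Background also describes earlier work in patients with disabilities in terms of unbalanced masseter and temporalis patterns and of balance regained after treatment.

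Four muscles are recorded: right and left masseter (RM, LM) and right and left anterior temporalis (RT, LT). Under Analysis of surface electromyography data, "the time domain analysis will be executed using the root mean square (RMS) of the EMG signal", in μV, normalised to the highest RMS in the maximum habitual intercuspation (MHI) and maximum voluntary contraction (MVC) readings. A frequency-domain analysis is also planned, with no variable named. Under Phases of the surface electromyography examination, "The obtained data will be compared among each group and among each person with themselves". Statistical analysis supplies the paired t or Wilcoxon test within groups and ANOVA or Mann–Whitney between groups. No left–right or masseter–temporalis quantity is defined anywhere in the article.

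**The concern.** Balance is a relation between muscles within one patient. RMS amplitude describes one muscle at a time. Averaging a muscle over patients before comparing sessions discards the relation. If the weaker side is the right in some patients and the left in others, evening-out raises the right masseter in some and lowers it in others, and the group mean need not move. Conversely, a general rise in amplitude moves every group mean and leaves the relation between sides as it was.

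At stake is whether the trial can answer one of the questions it poses. A non-significant amplitude result would not show that balancing failed, and a significant one would not show that it occurred.

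**Working it through.** **The plan's own figure.** The sample size section gives 10 per group for 90% power at two-sided 0.05, plus 5 per group for dropout. The total reproduces: 3 × (10 + 5) = 45. The 10 per group does not reproduce forwards, because no effect size or SD is stated. Solved backwards, n = 10 with 90% power corresponds to a paired standardised change of about 1.15. Nothing there refers to a balance measure.

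**Why the group mean can stand still.** All values in this model are assumptions: mean amplitude 100, weaker side 85, stronger side 115, between-patient SD 20, measurement SD 10, n = 10, 10,000 runs. Let p be the share of patients whose weaker side is the right. The index is A = 100 × |R − L| / (R + L), which starts at 100 × 30/200 = 15 before noise and ends at 0 when the sides meet.

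*Sides converge (weaker +15, stronger −15).* The mean change in the right muscle is 15p − 15(1 − p) = 15(2p − 1).

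| p | Mean change, right | Rejection, each side | Rejection, mean level | Rejection, index |
|---|---|---|---|---|
| 0.5 | 0 | 5–6% | 5% | 88% |
| 0.7 | 6 | 15% | 5% | 88% |
| 0.9 | 12 | 54% | 5% | 87% |
| 1.0 | 15 | 85% | 5% | 88% |

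*Only the weaker side rises, by 30, to meet the stronger.* The mean change in the right muscle is 30p, which is 15 at p = 0.5. Rejection at p = 0.5 is 52–53% for each side, 84% for at least one side, 99% for the mean level and 94% for the index.

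With 15 per group the pattern is the same. Convergence at p = 0.5 gives 5% per side against 98% for the index. A rise of the weaker side only gives 74–75% per side and 100% for the mean level.

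**A second model.** Log RMS of each side is a patient level ± a/2 plus noise. The sign of a is random, its SD is 0.15, the therapy halves a, and there is no net change in level (n = 10, 20,000 runs).

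| Side ratio | Noise SD (log scale) | Rejection, each side | Rejection, index |
|---|---|---|---|
| e^0.6 ≈ 1.8 | 0.10 | about 5% | 98% |
| e^0.6 ≈ 1.8 | 0.15 | about 5% | 77% |
| e^0.4 ≈ 1.5 | 0.10 | about 5% | 75% |
| e^0.4 ≈ 1.5 | 0.15 | about 5% | 41% |

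**The opposite error.** In this second model, let both sides rise by 0.25 on the log scale and leave the asymmetry unchanged. Per-muscle tests on log RMS then reject in 91–100% of trials and the index in about 5%.

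**Normalisation.** The article does not say whether the normalising maximum is taken per muscle. If it is, sides with maxima of 115 and 85 μV both become 100%, and A at maximal effort falls from 15 to 100 × 0/200 = 0. An index computed after that step could not see the difference. The simulations use unnormalised amplitudes, so they illustrate the mechanism and do not estimate power for the planned normalised variable.

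**The case against.** The strongest reply is that balance is not the only aim, nor clearly the leading one. The Abstract gives improved or restored muscle function and the sleep variables as primary outcomes. The mastication apparatus is meant to strengthen as well as modulate. Aims and hypotheses expects balance to come through fibre recruitment and less hypotonia, which is a change in level. The Discussion also puts level first and balance as a possible consequence. This stands: RMS suits the tone and strength aim, and under that mechanism the level tests would respond. They would be responding to level, however, and could not tell balancing from a uniform rise.

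A reader might go further in three ways that the article does not support.

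- *That a balancing therapy would test as no effect.* That needs a weaker side that varies between patients and no net change in level. The 85% per-muscle figure when the weaker side is always the same, and the 99% for mean level when only the weaker side rises, show how conditional it is.
- *That balance means left–right evenness.* The article never defines it. The Background wording could equally mean masseter against temporalis. No measure of that is defined either.
- *That the hope of near-normal muscle levels is untestable for want of a reference value.* Aims and hypotheses cites sources for physiologic patterns of muscle activity. They are not at hand, so the point cannot be made.

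It is also fair that a full protocol or SAP, not shown, might define an index. But the article does fix the derived EMG variable, down to the seconds discarded and the normalising maximum, and that variable does not match this aim. The frequency-domain analysis does not fill the gap, since spectral content is not a measure of balance.

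**Conclusion.** The point holds in a limited form. Balance is one stated masticatory aim among several, and no EMG variable in the article measures it. Tests on amplitude level cannot support a conclusion about balance in either direction. They can miss an evening-out (about 5% rejection against roughly 40–98% for an asymmetry index), and they can be significant with balance unchanged (91–100% against about 5%). The first contrast requires the weaker side to differ between patients and the stronger side to fall about as much as the weaker rises. If only the weaker side rises, the level tests reject in about 50% of trials per muscle and 99% for the mean level. Every percentage rests on assumed asymmetry and noise, because the article gives no EMG effect size or SD. The tone and strength aim is not affected.

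**What to change.** Under Analysis of surface electromyography data, add a within-patient balance index, computed for each patient and session before any averaging and on RMS in μV before any per-muscle normalisation:

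- 100 × |R − L| / (R + L) for the masseter pair and for the temporalis pair, at MVC and MHI;
- a masseter–temporalis ratio as well, if that is the balance meant, with its favourable direction stated.

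Name it as the EMG outcome for the balance aim, with a decrease in asymmetry as favourable. Keep normalised RMS and bite force for the tone and strength aim.

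The cost is small: a few lines in the signal-processing routine and some protocol wording, with no new recording, visit or patient. There are two downsides to state openly. Raw μV amplitudes are more sensitive to electrode placement and skin impedance than normalised ones. The sample size was not derived for this index, so the protocol should claim no power for it unless an effect size and SD are supplied.

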## Methods/design

This is a randomized, controlled, three-arm clinical trial conducted according to the ethical standards established in the 1961 Declaration of Helsinki (as revised in Hong Kong in 1989 and in Edinburgh, UK in 2000). This study was registered in the World Health Organization Universal Trial (UTN; number U1111-1201-3155) and Registro Brasileiro de Ensaios Clínicos (ReBEC; number RBR-3qp5np). It was also approved by the Brazilian Human Research Ethics Committee of the Institute of Science and Technology (CEPh 2.127.141; process number CAAE 64173616.4.0000.0077). All caregivers will be informed about the proposal therapies and will provide written informed consent. The whole study design (Fig. 1) and the SPIRIT checklist(aditional file 1) were followed. In addition, a SPIRIT figure is provided to illustrate the study schedule for the enrolment, interventions, and assessment (Fig. 2).

**Fig. 1 Fig1:**
[figure not shown]
Flowchart of study protocol

**Fig. 2 Fig2:**
[figure not shown]
SPIRIT figure: schedule for enrolment, interventions, and assessment. SPIRIT Standard Protocol Items: Recommendations for Interventional Trials

### Subjects

Adult patients with Down syndrome (DS), aged between 18 and 40 years, will be recruited from institutions for people with disabilities. The survey will be conducted at the Center for Bioscience Applied to Patients with Special Health Care Needs (CEBAPE), Institute of Science and Technology—UNESP/SJC, Brazil. The study will include adult patients with DS, from both genders, presenting subjective sleep disorder symptoms, snoring, and/or apnea/hypoapnea index (AHI) > 5.0/h, satisfactory dental health, and preserved cognitive function which allows them to understand and to respond to verbal commands necessary to perform this research project, and who agree to participate by free will including an Awareness Term signed by the patient or by the people responsible for the patient. The researchers will obtain informed consent from assistants, patients, and/or caregivers prior to the study. Cognitive analysis will be carried out under simple commands, such as “open your mouth”, “close your mouth”, “bite”, and “relax”. If patients are able to answer these simple commands, then they will be considered as part of the study. The exclusion criteria include body mass index > 30, use of psychiatric medication, inability to reach the university when needed, signs of psychiatric disease, and having been exposed to physiotherapy and/or orthodontic treatment at least 6 months prior to the beginning of this study.

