### Quality control

In order to ensure data quality, the dentists responsible for performing the EMG examination, as well as the sleep technicians responsible for the polysomnography examination, will receive appropriate training. External monitoring will be carried out periodically to verify the performance of EMG and polysomnography.

Guidance on the correct use and performance of each therapy will be given at each appointment, and all participants/caregivers will have access to an exclusive telephone number to solve any doubts they may have during the study, in order to avoid any misunderstanding that may compromise the results. This telephone contact will also be an instrument to reinforce the given guidelines and to encourage adherence to the therapies.

It will be explained to the participants/caregivers that they will be excluded whenever physiotherapy or speech therapy is to be undertaken during the study.

In addition, all participants/caregivers will be aware that they are free to withdraw their participation from this study at any time if they so wish, with no penalties.

If the participants face any difficulties to perform the proposed therapy, then they will be allocated to another therapy that they are able to perform.

The data obtained prior to and 2 months after all proposed therapies will be analyzed by “blind” evaluators. In addition, satisfaction, acceptance, and side effects will be assessed after a 2-month period, for each therapy applied.

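### As worded, the exclusion for earlier physiotherapy or orthodontics bars exposure six or more months back and admits people exposed only in the last six months

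*Protocol article*

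**What the plan says.** Under Subjects, the criteria that keep a person out begin: "The exclusion criteria include body mass index > 30, use of psychiatric medication, inability to reach the university when needed, signs of psychiatric disease". The last item in that list is having been "exposed to physiotherapy and/or orthodontic treatment at least 6 months prior to the beginning of this study". The clause is therefore a reason to reject a candidate, not a condition for entry.

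Quality control adds a rule for the trial period. Participants and caregivers are told that "they will be excluded whenever physiotherapy or speech therapy is to be undertaken during the study". This names physiotherapy and speech therapy, but not orthodontics. It covers only therapy taken up while the trial is running.

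On the use of the data, the section on the phases of the electromyography examination says: "The obtained data will be compared among each group and among each person with themselves". The Statistical analysis section tests the before-after change with a paired t test or a Wilcoxon test, and compares groups with ANOVA or the Mann–Whitney test. The Aims section gives each of the three groups an active therapy for two months.

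**The concern.** A six-month limit tied to the start of a study normally keeps out people whose condition may still be shifting after recent treatment. The clause as written does the opposite: it looks at exposure from six months back and earlier, and is silent on the most recent six months.

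This matters because masticatory muscle function is among the primary outcomes, and physiotherapy or orthodontics could plausibly act on it. If someone enters shortly after such treatment, the baseline recording may carry some of its effect. The change over two months then mixes the fading or persistence of the earlier treatment with the effect of the study therapy. A paired test within a treated group cannot separate the two, and the trial has no untreated arm to show what would have happened anyway. The groups are small: the Sample size section requires 10 per group, so one affected participant is 1/10 = 10% of a group of that size.

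**Working it through.** No arithmetic applies to the criterion itself, and the article gives no figure to reproduce. The check is a literal reading of the clause, followed by a search for text that corrects it.

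**Step 1: the clause as a rule.** Let t be the time from an exposure to the start of the study. At least six months prior means t ≥ 6 months. As an exclusion, the rule rejects anyone with any exposure at t ≥ 6 months and accepts anyone whose exposures all lie at t < 6 months. It sets no upper limit on t.

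**Step 2: example histories.** The histories are illustrations. The right-hand column shows a rule that excludes any exposure at t < 6 months.

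| Exposure history | Rule as written | Recent-treatment rule |
|---|---|---|
| None | eligible | eligible |
| Only 8 months before start | excluded | eligible |
| Only 1 month before start | eligible | excluded |
| At 8 months and again at 1 month | excluded | excluded |
| Continuous from 8 months to 1 month before start | excluded | excluded |

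The two rules disagree in the second and third rows, and in opposite directions. They agree in the last two because the clause speaks of having been exposed, not of when treatment ended. A long course that stopped last month is still caught, through its earlier part.

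**Step 3: whether another section repairs it.** No other section of the article restates the criterion or gives a look-back window. The Quality control rule removes people who undertake physiotherapy or speech therapy during the trial. It does not reach physiotherapy that began less than six months before the start and stopped before enrolment. It does not name orthodontics at all.

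**Step 4: the two therapy lists.**

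| Therapy | Before the study (Subjects) | During the study (Quality control) |
|---|---|---|
| Physiotherapy | named | named |
| Orthodontics | named | not named |
| Speech therapy | not named | named |

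Only physiotherapy appears in both. The article does not say whether the difference is intended.

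**The case against.** The strongest reply is that nobody would apply the clause literally. The English of the article is not idiomatic in places, and the phrase can be taken as a loose way of stating a look-back of at least six months. A rule that turns away someone treated years ago and accepts someone first treated last week serves no evident purpose, so staff may well apply the sensible meaning. The article also never states that the clause is a wash-out; that purpose is inferred. These points stand. They make this a wording defect and not evidence of how the trial was run. They do not remove it, because eligibility has to be applied in the same way to every candidate and the text on the page says something else.

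A second reply is that the harm is limited. Concurrent physiotherapy and speech therapy are barred, and randomisation does not tie residual effects to one arm. This also stands in large part. The exposed comparisons are mainly the within-person ones, although with groups this small randomisation cannot be relied on to spread a few such people evenly.

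A reader might go further and infer three things that the article does not support:

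- **That anyone whose treatment stopped recently gets in.** The word used is exposed, so a course that reached back six months or more is still excluded.
- **That the rule would reject a large share of candidates and endanger recruitment of 45.** The article gives no figure for past physiotherapy or orthodontics in this population, so any percentage would only restate an assumption.
- **That the two therapy lists contradict each other.** They govern different periods and may differ on purpose. The point is only that the sponsor should say so.

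**Conclusion.** The criterion is wrong as written. Its literal effect is to exclude exposure from six months back without limit, and to admit people whose only exposure lies within the last six months. Nothing else in the article corrects it.

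The size of any effect on the results cannot be calculated, because the article does not say how many candidates have such a history or how long residual effects last. The conclusion about the wording rests on the text alone. Two further statements rest on inference: that a recent-treatment exclusion was intended, which follows from the six-month limit and the bar on concurrent therapy; and that recent treatment could affect muscle recordings, which is plausible but not quantified. The defect should be corrected because the before-after comparisons depend on a stable baseline and have no untreated arm behind them.

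**What to change.** If a recent-treatment exclusion is meant, reword the last exclusion item so that it covers exposure to physiotherapy and/or orthodontic treatment within the six months before the start of the study. If something else is meant, state the window explicitly, with both ends.

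Separately, the sponsor should confirm whether the therapy lists in Subjects and Quality control are meant to differ, and in particular whether speech therapy before the study and orthodontics during it were left out on purpose.

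The cost is one sentence in the eligibility criteria and a short confirmation about the lists. The downside is negligible.
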